### Participants and recruitment

Eighty-four participants will be recruited from the rehabilitation hospital affiliated with the Fujian University of Traditional Chinese Medicine in Fuzhou, China. Participants will be recruited by distributing leaflets, posters and recruitment information on WeChat or other online platforms. Interested volunteers can contact the research assistant, who will screen applicants according to the inclusion and exclusion criteria. The research assistant will provide the consent form to each participant (see Additional file 5). This form provides fundamental information about the research, including the goals, the inclusion and exclusion, and potential adverse events. At the same time, the research assistant will explain that each participant will be randomly assigned to the control or Tai Chi group. Each participant must agree that if they are randomly assigned to the control group, he/she will not participate in Tai Chi. Eligible volunteers will be invited to join the study, sign the informed consent form, and then arrange the baseline assessment.

#### Inclusion criteria

To be eligible to participate in the study, each participant must meet the following criteria:Meet the diagnostic criteria of ‘stroke’ in the diagnostic essentials of various cerebrovascular diseases adopted at the Fourth National Cerebrovascular Disease Academic Conference in 1995 and confirmed by head computed tomography or magnetic resonance imaging;The first stroke occurred between 2 weeks and 6 months prior to commencing the study;Unilateral cortical lesion (left or right hemisphere) or subcortical lesion involving the motor pathway;The muscle strength of the upper limb of the affected side is ≥ 3 and muscle tone is ≤ 2 based on the Modified Ashworth Scale (MAS);Right-handedness before stroke;Age between 50 and 70 years;Blood pressure stable and below 160/100 mmHg;A Mini-Mental State Examination (MMSE) score of > 17 points for illiterate participants, > 20 points for participants with a primary school education, and > 24 points for participants with a middle school and above education;Brunnstrom stage ≥ IV in the affected upper limb;Standing balance ≥ level 2, the ability to stand independently for more than 5 min, and the ability to walk independently for more than 6 m;Willing to sign the informed consent form and understand, accept, and implement the rehabilitation guidance.

#### Exclusion criteria

The exclusion criteria for participants were:Upper limb motor dysfunction caused by other diseases such as brain tumours, brain injury, or parasitic brain disease;Diseases affecting the ability to participate in Tai Chi training: serious lower limb joint diseases, arthritis, joint injury, cervical spondylotic myelopathy, lumbosacral spinal canal stenosis, and lower limb neuropathy;Severe complications of stroke, such as severe pulmonary infection, shoulder hand syndrome, or venous embolism of lower limbs;Severe heart disease; heart, liver, and kidney failure; malignant tumours; and gastrointestinal bleeding;MMSE score ≤ 17 points for illiterate participants, ≤ 20 points for participants with a primary school education, and ≤ 24 points for participants with a middle school and above education;Severe visual impairment and cannot complete the training;Sensory aphasia (unable to understand the instructions);Participation in Tai Chi training within the past 6 months;Contraindications for near-infrared functional imaging and EEG, such as skin infection, scalp wound, dermatitis, and metal implants under electrodes;Skin or muscle lesions of extremities that affect surface EMG;Unable to cooperate or not suitable to participate in the examination, evaluation, and treatment of this study for other reasons, such as intolerable pain, abnormal mental state, or limited ability to move; Participation in other clinical studies.

#### Dropout criteria

Participants will be withdrawn from the trial for the following reasons:Subjects who experience severe adverse events and are not suitable for the trial;Subjects who suffer another stroke;Subjects who voluntarily withdraw from the trial; Subjects with deterioration or severe complications and who need emergency intervention measures.

### Randomization and allocation concealment

After baseline assessment, eligible participants will be randomly assigned to the Tai Chi group or the control group in a 1:1 ratio. Random assignment sequences will be generated by independent statisticians using the SAS 9.1 statistical software. Opaque, sealed envelopes will hide the randomization sequence, and participants will be managed by an independent research assistant who will know nothing about recruitment, evaluation, and intervention. The independent research assistant will inform the eligible participants of their assignment results by telephone.

### Blinding

In this study, it will be impossible to blind the Tai Chi coaches and participants regarding the treatment. However, all statisticians and evaluators will be blind regarding the group assignments. This study will use a two-level blinding method: the first level uses the letters ‘A’ and ‘B’ to represent the group to which the participant is assigned, and the second level uses the letters ‘A’ and ‘B’ to represent the intervention measures, namely Tai Chi and control. At the end of the study, the data will be entered into the database according to the participant’s codes. After data entry, the database will closed and primary unblinding will be performed to determine which group of participants are assigned to ‘A’ and ‘B’. After completing all data analysis, secondary unblinding will be performed to determine whether the subjects are assigned to the Tai Chi or the control group.

### Intervention

#### Control group

The control group will receive routine medical treatment, health education, and rehabilitation training. According to the 2014 guidelines for the secondary prevention of ischaemic stroke and transient ischaemic attack in China, formulated by the cerebrovascular disease group of the neurology branch of the Chinese Medical Association in 2015, the subjects will receive routine medical care, including aetiological treatment, blood pressure management, antiplatelet therapy, anticoagulation therapy, essential treatment of heart disease, hyperglycaemia treatment, and blood glucose and lipid management. According to published guidelines [34], the following health education will be given to subjects: (1) emphasize the severe harm of stroke so that the patients can consciously take active preventive measures; (2) the principal risk factors and inducing factors of stroke and how to carry out secondary prevention; and (3) coping with stroke and rehabilitation. The therapist will conduct rehabilitation training for the subjects according to the guidelines [35]. The participants will receive rehabilitation treatment by trained occupational therapists for the affected upper limb; it will consist of five 60-min sessions per week, for a total of 20 total sessions.

During the entire 4-week intervention, all subjects will record the duration of activities each day (classified as static work, low-intensity activity, medium-intensity activity, and high-intensity activity), their diet, and the drugs they take.

#### Tai Chi group

This group will receive Tai Chi training, routine medical care, health education, and rehabilitation training. The routine care, education, and rehabilitation training will be the same as described for the control group. The Tai Chi training will be led by Tai Chi coaches with more than 5 years of qualification. Tai Chi training follows a gradual process from part to whole and from easy to complex. The teacher will choose the appropriate form of Tai Chi according to each participant’s ability. When adjusting Tai Chi training for each participant, two fundamental principles are used: (1) the participant should be able to practice Tai Chi while relaxing and (2) there should be as much overall coordination as possible. The participant relaxes his/her muscles and joints as much as possible and focuses on movements that help him/her relax, completing these movements with minimal effort. The movement is slow, repetitive, and, if necessary, carried out in sections. Eight Tai Chi poses will be adopted in this study: Starting Posture, Parting the Wild Horse’s Mane on both sides, Brush Knee and Twist Step on both sides, Forearm Rollings on both sides, Grasp the Bird's Tail – Left Side, Grasp the Bird's Tail – Right Side, Cloud Hands, and Closing Form. These poses have been selected based on the literature [4, 36]. Please refer to 24 simplified standard movements of Tai Chi promoted by the General Administration of Sport (http://www.sport.gov.cn/). In the actual training process, the accuracy and consistency of the posture routine will not be emphasized. At the same time, according to the actual movement ability of the patient, the difficulty of reaching the posture standard will be appropriately reduced. The participants will receive five 60-min sessions per week, for a total of 20 sessions. Each session will include 5 min of warm-up, 50 min of Tai Chi training, and 5 min of cooldown. The training will be conducted at Fujian provincial rehabilitation hospital. The researchers involved in this trial will not carry out relevant concomitant care and interventions that are permitted or prohibited during the trial.

### Outcome measurements

The variables of this trial include basic characteristics, primary and secondary outcomes, and exploratory results. The basic characteristics will be determined from a questionnaire administered at baseline (1–2 weeks before randomization). The primary and secondary outcomes will be measured at baseline and at the end of the intervention (4 weeks after randomization). The exploratory results will be measured at baseline and at the end of the intervention (4 weeks after randomization). All results will be assessed by experienced assessors who do not know the group assignments of the participants.

#### Primary outcome measures

The primary outcome measure is the change in the FMA-UE scale score from baseline to the end of the 4-week intervention. The FMA-UE scale includes 33 items divided into four subscales (arm, wrist, hand, and coordination), each scored on a 3-point sequential scale [37]. Scoring is based on performing independent actions inside and outside the synergy pattern. The maximum score of 66 corresponds to undamaged motor function. The FMA-UE scale is often used to classify the severity of stroke injury, and the scale shows good reliability and validity. A FMA-UE score between 32 and 57 indicates moderate upper limb injury and an FMA-UE score between 58 and 65 indicates mild injury of the contralateral arm. FMA-UE sensation (0–12), passive range of motion, and pain (0–24) will also be assessed.

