#### Secondary outcome measures

Kinematic analysis includes endpoint performance parameters, joint angle, shoulder/elbow coordination index, and trunk compensatory motion. Two Kinect motion capture systems will be used for a kinematic evaluation to analyse the three-dimensional motion of the trunk and upper limbs while reach-to-grasp-pen and Tai Chi Cloud Hand. During the measurement process, the camera unit with high spatial resolution immediately calculates the three-dimensional (3D) coordinates of the mark. The Kinect SDK automatically collects data. The captured data are transferred to MATLAB software for customized analysis. Azure Kinect records XYZ coordinate data of 25 anatomical landmarks at a sampling frequency of 30 Hz. These landmarks, which do not require markers, include the head, neck, spine, left and right shoulders, left and right elbows, left and right wrists, left and right hands, left and right fingertips, left and right thumbs, middle ridges, left and right hips, left and right knees, left and right ankles, and left and right feet. To ensure stable mark recording, Azure Kinect is placed on a tripod with a height of 114 cm, an inclination angle of 20°, and a distance of 140 cm from the far end of the table. The table and chair are 75 cm and 46 cm high, respectively. The participant sits comfortably on the chair in front of Kinect and naturally completes the tasks of reach-to-grasp-pen with their upper limbs and Tai Chi Cloud Hand at their own pace. The participant is encouraged to follow the guidance video and repeat each task five times. No additional assistance is provided to the subjects unless there are safety issues.

The Modified Ashworth Scale (MAS) will be used to evaluate the change in passive motor resistance and spasm [38]. This 6-point sequential scale will be used to measure tone in the scapular adductor, elbow, wrist, and finger flexors at rest; the score ranges from 0 (muscle tension does not increase) to 4 (the affected part is stiff during flexion or extension). A MAS score of ≥ 1 in one or more muscles indicates a spasm.

The Wolf Motor Function Test (WMFT) will be used to evaluate the functional activity of the upper limbs [39]. The WMFT consists of 15 items. Items 1–6 are simple joint movements while items 7–15 are compound functional movements. The WMFT score is determined based on the quality of all actions (0–5 points, six grades).

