### Safety evaluation

During the study intervention, any adverse events that occur the subjects will be monitored, recorded on the adverse event case report form (CRF), and then reported to the research assistant. The causal relationship between Tai Chi training and the severity of adverse events will be analysed. Adverse events are defined as any dysfunction caused by the intervention, such as knee or ankle sprain, knee pain, or hypoglycaemia. In the case of any adverse event, the coach or project manager will provide complementary treatment for the participants. Serious adverse events will be reported to the rehabilitation hospital’s ethics committee affiliated with the Fujian University of Traditional Chinese Medicine. Additional file 5 provides additional details.

The safety of subjects will be evaluated based on several factors. The evaluation results are divided into level 1 (safe, no adverse reactions); level 2 (safe but with mild adverse reactions that do not require treatment; subjects can continue to participate in training); level 3 (safety problems and moderate adverse reactions, but the subjects can continue training after receiving treatment); and level 4 (study terminated due to severe adverse reactions) (Common Terminology Criteria for Adverse Events [CTCAE] version 5.0, US Department of Health and Human Services, 2017).

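### FMA-UE pain and passive range, scored by blinded assessors, have no stated analysis or safety role, while adverse events count only if attributed to the intervention

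*Protocol article*

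**What the plan says.** **Scores collected.** The Primary outcome measures section describes the FMA-UE motor score, for which "The maximum score of 66 corresponds to undamaged motor function". It then adds that "FMA-UE sensation (0–12), passive range of motion, and pain (0–24) will also be assessed". The Outcome measurements section states that "All results will be assessed by experienced assessors who do not know the group assignments of the participants".

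**Outcome classes.** The same section says "The variables of this trial include basic characteristics, primary and secondary outcomes, and exploratory results". Safety is not among these classes. Pain and passive range do not appear under Secondary or Exploratory outcome measures.

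**Adverse events.** Safety evaluation says events are monitored during the study intervention, entered on an adverse event form and passed to the research assistant. It defines an event as dysfunction attributed to the intervention, with the examples "such as knee or ankle sprain, knee pain, or hypoglycaemia". The causal analysis concerns Tai Chi training. The lowest safety level means no adverse reactions. The rating draws on factors that are not listed, and Additional file 5, which is not shown, is cited for more detail.

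**Spasticity.** Secondary outcome measures says "The Modified Ashworth Scale (MAS) will be used to evaluate the change in passive motor resistance and spasm".

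**Contact and blinding.** Both arms receive 20 occupational therapy sessions for the affected arm. The Tai Chi arm receives 20 further 60-minute sessions led by coaches, which the Discussion says two research assistants supervise. The Blinding section says coaches and participants cannot be blinded.

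**The concern.** The trial adds movement training in patients with a weak arm, so arm pain and loss of passive range are natural harms to look for. Two sources of information exist. One is the event list, which depends on someone noticing a problem and attributing it to the intervention. The other is a pair of scores taken by blinded assessors in every participant, which need no judgement of cause. The article relies explicitly on the first and says nothing about how the second will be used.

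Attribution is the weak step. New shoulder pain after stroke can readily be ascribed to the stroke, and then it is not an event under the stated definition. Control participants receive no Tai Chi, so it is unclear how an event in that arm would qualify or enter the causal analysis. Event counts from two arms with different amounts of supervision and an attribution filter are hard to compare, and the bias could run in either direction. The Discussion seeks a safe treatment, and a claim of safety would rest on those counts. If the scores have no assigned use, whether to report them becomes a choice made after the data are seen.

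**Working it through.** The point rests mainly on setting sections side by side.

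1. *Are pain and passive range inside the primary outcome?* No. The primary score has a maximum of 66 for motor function, and these domains are named separately.
2. *Are they in another analysed class?* Not in the article. Statistical analyses covers primary and secondary outcomes, and later sections cover the kinematic and the fNIRS, EEG and EMG data. Pain and passive range are in none of these.
3. *Are they named in Safety evaluation?* No. They are not ruled out either, because the factors behind the rating are unspecified.
4. *Would a new arm problem be an event?* Only if judged to result from the intervention. The examples are illustrative, so an arm event is not excluded, but none is given.
5. *Would a control-arm problem be counted?* The definition does not restrict events to one arm, but the causal analysis refers to Tai Chi training only.
6. *Is observation equal?* Both arms have 20 therapy sessions. The Tai Chi arm has 20 + 20 = 40 supervised sessions against 20.

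**Precision of the comparison that could be made.** Sample size estimation gives 42 per arm and 20% dropout: 42 × 0.8 = 33.6, taken as 34 per arm.

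- The 95% CI half-width for a difference in means, in SD units, is t(0.975, 2n − 2) × √(2/n).
- n = 34: 1.997 × √(2/34) = 1.997 × 0.2425 = 0.48 SD.
- n = 42 (no dropout): 1.989 × √(2/42) = 1.989 × 0.2182 = 0.43 SD.

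The document gives no SD for either score, so this cannot be turned into points. An ordinal score with many participants at no pain would also fit the normal approximation poorly, which is one reason to report the number worsened as well.

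**What an empty event list would mean.** With zero events in n participants, the one-sided 95% upper limit for the risk is 1 − 0.05^(1/n). This is 6.9% for n = 42 and 8.4% for n = 34. These limits follow from any zero count of that size. They show that an empty list reassures only modestly, not that harm is missed here.

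**The case against.** The strongest reply is that this is largely silence in a condensed article. The safety rating draws on unlisted factors, a supplementary file is cited, and a full protocol may assign these scores a use. That stands in part: a reader might infer that the scores have no safety role at all, and the article shows only that none is stated. The reply does not reach the adverse event definition, which is printed and makes attribution a condition of counting.

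Other stronger readings also go beyond the text:

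- *Safety rests on unblinded reports made during training.* The article says monitoring runs during the study intervention and does not name who detects or records events. Unblinded reporting is likely, because coaches and participants know the allocation, but it is an inference.
- *Nobody watches the control arm.* Therapists work on the affected arm in both groups five times a week, and all participants keep daily logs of activities, diet and drugs taken. The imbalance is one of degree.
- *Worsening spasticity could be hidden.* MAS is a secondary outcome, and Statistical analyses compares secondary outcomes between arms.
- *The entry criteria show that arm pain is a recognised hazard.* The exclusion list names severe stroke complications "such as severe pulmonary infection, shoulder hand syndrome, or venous embolism of lower limbs", and intolerable pain appears as a reason for being unable to cooperate. Neither is a statement about arm pain from training.
- *The harm goes unmeasured.* It is measured; what is missing is a prespecified use.

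It is also fair that blinding protects the scores only in part, since an unblinded participant reports the pain, and that week-4 timing for these domains is inferred from their place under the primary outcome.

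**Conclusion.** The concern holds in a limited form. The article collects pain and passive range through blinded assessors in both arms and states no class, analysis or safety use for them. Its adverse event definition lets arm worsening ascribed to the stroke, or occurring in the control arm, go uncounted. Followed as written, a rating of no adverse reactions could stand while those scores worsened more in one arm.

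The amount of harm that might be missed cannot be sized, because the document gives no event rate and no SD for the scores. What can be sized is the comparison available from planned data: about ±0.48 SD with 34 per arm, enough to show a large difference but not to exclude a moderate one. This assumes that the domains are scored at baseline and week 4 like the motor score, that 20% drop out evenly, and that no unseen document already assigns the scores a safety role. The change is worth making because it is cheap, not because harm has been shown.

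**What to change.** 1. Name change from baseline to week 4 in FMA-UE pain and passive range as prespecified safety outcomes, and state the assessment times. Report the arm difference with a 95% CI and the number worsened in each arm, noting that pain is reported by unblinded participants.
2. In Safety evaluation, define adverse events regardless of presumed cause. Judge causality as a separate step, by the same procedure in both arms.
3. Record new or worsened arm pain found at week 4 on the adverse event form in both arms. This needs the revised definition in item 2, because the present one would filter such findings out.
4. MAS needs at most a cross-reference from the safety table to the secondary outcome analysis.

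The cost is one extra table, revised wording, a small added recording step at week 4 and somewhat more event recording. No new visit or measurement is needed, provided the scores are already taken at both times. The changes should be fixed before unblinding.

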#### Secondary outcome measures

Kinematic analysis includes endpoint performance parameters, joint angle, shoulder/elbow coordination index, and trunk compensatory motion. Two Kinect motion capture systems will be used for a kinematic evaluation to analyse the three-dimensional motion of the trunk and upper limbs while reach-to-grasp-pen and Tai Chi Cloud Hand. During the measurement process, the camera unit with high spatial resolution immediately calculates the three-dimensional (3D) coordinates of the mark. The Kinect SDK automatically collects data. The captured data are transferred to MATLAB software for customized analysis. Azure Kinect records XYZ coordinate data of 25 anatomical landmarks at a sampling frequency of 30 Hz. These landmarks, which do not require markers, include the head, neck, spine, left and right shoulders, left and right elbows, left and right wrists, left and right hands, left and right fingertips, left and right thumbs, middle ridges, left and right hips, left and right knees, left and right ankles, and left and right feet. To ensure stable mark recording, Azure Kinect is placed on a tripod with a height of 114 cm, an inclination angle of 20°, and a distance of 140 cm from the far end of the table. The table and chair are 75 cm and 46 cm high, respectively. The participant sits comfortably on the chair in front of Kinect and naturally completes the tasks of reach-to-grasp-pen with their upper limbs and Tai Chi Cloud Hand at their own pace. The participant is encouraged to follow the guidance video and repeat each task five times. No additional assistance is provided to the subjects unless there are safety issues.

The Modified Ashworth Scale (MAS) will be used to evaluate the change in passive motor resistance and spasm [38]. This 6-point sequential scale will be used to measure tone in the scapular adductor, elbow, wrist, and finger flexors at rest; the score ranges from 0 (muscle tension does not increase) to 4 (the affected part is stiff during flexion or extension). A MAS score of ≥ 1 in one or more muscles indicates a spasm.

The Wolf Motor Function Test (WMFT) will be used to evaluate the functional activity of the upper limbs [39]. The WMFT consists of 15 items. Items 1–6 are simple joint movements while items 7–15 are compound functional movements. The WMFT score is determined based on the quality of all actions (0–5 points, six grades).

The Stroke Impact Scale (SIS) is used to assess the overall quality of life of post-stroke patients [40]. The assessment includes a series of self-reported questions that assess the quality of life related to strength, hand function, mobility, and activities of daily living. The instrument provides a total score from 16 points (maximum injury) to 80 points (minimum injury).

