## Methods/design

### Study design

A randomized, single-blind, parallel-controlled trial will be conducted to evaluate the effectiveness and neural mechanism of traditional Tai Chi training in stroke patients with upper limb dysfunction. The framework of this trial is a superiority trial design. The evaluators and data analysts will be blinded regarding the treatment. A total of 84 eligible participants will be randomly assigned to the Tai Chi group or the control group in a 1:1 ratio. Members of the Tai Chi group will receive 4 weeks of Tai Chi training five times a week, with each session lasting for 60 min (a total of 20 sessions). Participants in the control group will not receive Tai Chi training. Both groups will receive medical treatment and routine rehabilitation training. The primary and secondary outcomes will be measured at baseline and 4 weeks (the end of intervention). This study will use the SPIRIT reporting guidelines [32] (see Additional file 3 for more details). The flow chart of the research design is shown in Fig. 1, and the enrolment, intervention and assessment schedule is shown in Fig. 2. Additional file 4 shows additional details.

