### fNIRS-EEG-EMG experimental paradigm

There will be three tasks: upper limb forward reach, elbow flexion and extension, and Tai Chi Yunshou. After a 3-min rest period (baseline), the motor paradigm will use a three block design:Upper limb forward reach with three cycles of preparation [3 s] – reach forward [3 s] – rest [3 s];Elbow flexion and extension with three cycles of preparation [3 s] – elbow flexion [3 s] – rest [3 s] – elbow extension [3 s] – rest [3 s];Tai Chi Yunshou with three cycles of preparation [3 s] – Tai Chi Yunshou [3 s] – rest [3 s]

For each motor task, there will be 3 s of preparation. The subjects will be asked to perform specific motor tasks for 3 s according to the instructions and then relax for 3 s. Each motor task will consist of 20 repetitions. The tests will be carried out on both sides of the arm of post-stroke patients. Each subject will use his/her left and right hands to perform each motor task. He/she will take a 5-min break between each task to prevent muscle fatigue. The experiment will last for 30 min for each subject (2 hands × 3 tasks × 20 repetitions). Finally, the static state will be assessed for 3 min. Data will be collected at baseline and after the 4-week intervention.

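### Cloud Hands is trained only in the Tai Chi arm yet is also a test task, so a between-arm difference on it mixes practice with motor recovery

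*Protocol article*

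**What the plan says.** All references are to the protocol article.

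- **Test task, kinematics.** Under Secondary outcome measures, two Kinect systems are to analyse "the three-dimensional motion of the trunk and upper limbs while reach-to-grasp-pen and Tai Chi Cloud Hand". The indices are endpoint performance, joint angle, shoulder/elbow coordination and trunk compensation. Participants sit, follow a guidance video and repeat each task five times at their own pace.
- **Test task, neurophysiology.** The fNIRS-EEG-EMG paradigm states: "There will be three tasks: upper limb forward reach, elbow flexion and extension, and Tai Chi Yunshou".
- **Training.** The Tai Chi group section ends its list of eight poses with "Grasp the Bird's Tail – Right Side, Cloud Hands, and Closing Form". There are 20 sessions, and "Each session will include 5 min of warm-up, 50 min of Tai Chi training, and 5 min of cooldown".
- **Controls.** Study design: "Participants in the control group will not receive Tai Chi training". Under Participants and recruitment, agreeing to this is a condition of entry.
- **Prior exposure.** One exclusion criterion is "Participation in Tai Chi training within the past 6 months", so neither arm starts with recent practice.
- **Use of the results.** The Background says the kinematic changes will serve to tell recovery from compensation. The analysis section for fNIRS, EEG and EMG compares change in connectivity between arms. It then selects brain regions that differ between arms and correlates their features with upper limb scores.
- **Blinding.** Outcome measurements: "All results will be assessed by experienced assessors who do not know the group assignments of the participants". The Blinding section accepts that participants and coaches cannot be blinded.

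**The concern.** One test task is a movement that a coach teaches in one arm and that the other arm agrees not to practise. A better week-4 performance in the Tai Chi arm could come from a recovered limb, from having learned that movement, or from both. The task alone cannot tell these apart, yet telling recovery from compensation is what the kinematic outcome is for.

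Training and scoring also overlap in content. The coaching principles stress whole-body coordination and slow movement with little effort, and the scored indices include a coordination index and trunk compensation.

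The same difficulty reaches the mechanism work. If connectivity recorded during Yunshou differs between arms because of practice, that difference could influence which regions are selected for correlation with upper limb scores.

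There is a second, smaller concern. An assessor who watches Cloud Hands at week 4 may get a hint of the allocation. FMA-UE, the primary outcome, and WMFT are both rated by an observer.

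**Working it through.** The plan gives no figure for the kinematic outcome or for a practice effect. The check therefore sets the sections side by side, then adds simple arithmetic and a labelled illustration.

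**1. Is the test movement trained in one arm only?** The Tai Chi group section lists it among the trained poses ("Cloud Hands, and Closing Form"). Study design, together with Participants and recruitment, excludes it for controls. Yes.

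**2. Which tasks are affected?**
- Kinematics: Cloud Hand is affected, one of two tasks. Reach-to-grasp-pen is not among the eight poses.
- fNIRS-EEG-EMG: Yunshou is affected, one of three tasks. Forward reach and elbow flexion/extension are not among the eight poses.

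The article does not define Yunshou; it is taken here as another name for Cloud Hands. If it were a different movement, the kinematic part of the point would be unchanged.

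**3. Does the plan keep the trained task apart?** No section separates the Cloud Hand result from the reach result. None says which tasks feed the region selection. None sets the test order or gives the task to a separate assessor.

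**4. How different is the exposure?**
- Tai Chi arm: 20 sessions × 50 min = 1000 min = 16.7 h of Tai Chi. With equal time per pose (an assumption), 1000 / 8 = 125 min, about 2 h, on Cloud Hands.
- Both arms, at baseline testing: five Kinect repetitions, plus 20 repetitions with each hand in the neurophysiology session. That is 2 × 20 = 40 repetitions of 3 s each, or 120 s of movement.

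Controls therefore have some exposure, but much less.

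**5. What could a practice effect do?** Suppose there is no true difference in recovery, and practice alone shifts a Cloud Hand index by a given number of SDs. The table gives the chance of a significant between-arm difference (two-sided t test, alpha 0.05). The first sample size is the planned 42 per arm. The second allows for the plan's 20% dropout: 42 × 0.8 = 33.6, taken as 34.

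| Assumed practice effect | 42 per arm | 34 per arm |
|---|---|---|
| 0 SD | 5% | 5% |
| 0.2 SD | 15% | 13% |
| 0.3 SD | 27% | 23% |
| 0.5 SD | 62% | 53% |
| 0.8 SD | 95% | 90% |

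The effect sizes are assumptions; the documents support none of them over the others. The table applies to an index measured on the trained task only.

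**The case against.** The best defence is that a mechanism study may reasonably record the trained movement, provided it is read beside untrained ones, and the plan already collects those. No section rests a recovery claim on Cloud Hands alone, and task-by-task reporting is often left to an analysis plan, which is not shown. Both arms follow the same video, and Kinect capture is automatic. This stands in part. It shows that the repair is easy, and that rater bias in the kinematic values themselves is limited. It does not remove the practice difference, and the choice of task is fixed in the outcome section itself.

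A reader might infer more than the article supports:

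- **That a Cloud Hand difference shows skill and not recovery.** The indices can change through either, so the supportable statement is that the two are mixed.
- **That a positive result is to be expected without recovery.** This needs a moderate or large practice effect, and none is given. At 0.2 SD the chance is only 15% with 42 per arm.
- **That fluent performance reveals the allocation and so breaks the FMA-UE blind.** The test is seated, self-paced and video-guided. In training, precise form is not stressed and difficulty is adapted to ability, so fluency is an imperfect cue. Harm to FMA-UE or WMFT also requires the same assessor to rate them after seeing the task. The article is silent on this, and the research manual mentioned under Quality control may settle it.
- **That controls have no exposure.** They perform the task at baseline.
- **That a confirmatory result is at stake.** Kinematics are secondary and neurophysiology is exploratory. Nothing in the description of FMA-UE makes Cloud Hands one of its items.

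**Conclusion.** The point holds for one of two kinematic tasks and, reading Yunshou as Cloud Hands, for one of three neurophysiology tasks. On these, a between-arm difference combines task-specific practice with any motor recovery. It cannot by itself carry the recovery-versus-compensation interpretation or the mechanism claim. The untrained tasks are not affected in this way, and the FMA-UE items as described are not directly practised.

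The difference in practice is large if poses share the time equally: about 2 h against brief test exposure. Time per pose is not stated, however, and the coach adapts the forms to the participant. Hours of practice do not convert into a bias, so its size remains unknown.

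The risk to assessor blinding is a possibility only. It depends on test order and assessor allocation, which the article does not state.

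The change should be made. The overlap is certain from the text and the remedy uses data already being collected.

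**What to change.** 1. Base the between-arm kinematic secondary comparison on reach-to-grasp-pen.
2. Base the mechanism inference on forward reach and elbow flexion/extension. This includes the selection of regions for correlation with upper limb scores.
3. Report Cloud Hands/Yunshou separately, labelled as a measure of task-specific learning that does not support a recovery claim.
4. For participants not yet assessed, record Cloud Hands/Yunshou after FMA-UE, WMFT and the other rated assessments. If the research manual already fixes this order or uses separate assessors, stating so is enough.

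**Cost.** Outcome and analysis wording, which can be settled before the final analysis, and the order of tests. No procedure or visit is added. The sponsor gives up Cloud Hands as a contributor to the secondary recovery claim, and Yunshou as a basis for mechanism inference. The new order cannot help participants whose week-4 assessment is already done.
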